### Management before procedure

Before the start of the study, NICU nurses will undergo training in the theory of and technical training in kangaroo care and breastfeeding in preterm infants. On the day of admission, eligibility will be determined according to the inclusion and exclusion criteria. The breastfeeding education nurse conducts breastfeeding education and sends the Hospital Anxiety and Depression Scale anxiety subscale (HAD) [37] questionnaire to the mother for completion within 24 h by WeChat, China’s predominant social media platform. The questionnaire will be withdrawn and made unavailable after 24 h. After admission, respiratory support, enteral and parenteral nutrition, lactation volume, and weight will be recorded daily until the infant is discharged home.

### Consent

Explanations are made with consideration of potential emergency situations, and explanations of the purpose, methods, and possible expectations of the study are made to the mothers who meet the inclusion criteria. Informed consent will be obtained from parents.

### Interventions

#### The control group

After withdrawing mechanical ventilation, before each feed, a pacifier is used for 5–10 min of non-nutritive sucking. Feeds are given with a special bottle designed for preterm infants. Body weight is measured before the first oral feeding is given. When oral feeding is commenced, the infant’s mother will be informed by telephone that this has started. At this point, the HAD questionnaire is sent to the mother for a second time for completion within 24 h. According to the oral feeding schedule, the frequency of oral feeds is gradually increased. Full oral feeding is considered established when the daily amount of oral feeding milk reaches 75% of the required volume, no gavage feeding is needed for 48 h, and the daily body weight increases by 10–15g/kg/day. At this time, the infant is weighed, the mother is informed by phone, and the HAD questionnaire is sent to the mother for the third time for completion within 24 h. The weight will be measured again on the day of discharge, and parental satisfaction will be assessed by EMPATHIC-N [38]. On discharge, the HAD questionnaire was sent to the mother for the fourth time for completion within 24 h. And the PIBBS scale will be used to evaluate the breastfeeding behavior of preterm infants on discharge day. The research team members will organize and enter data on the infant’s clinical course in the hospital, and a second-team member will be responsible for verifying the data collection and entry. After discharge, the rate and mode of breastfeeding will be followed up by breastfeeding education nurses at 3 and 6 months corrected gestational age.

#### The intervention group

After the withdrawal of mechanical ventilation, the infant will be assessed for 12 to 24 h and participants in the intervention group would receive a combination of skin-to-skin contact and breastfeeding. When the infant’s condition is stable, the mother will be invited to enter the NICU, and the HAD questionnaire will be sent to the mother for the second time for completion within 24 h. Before SSC, the mother pumps and expresses breast milk for about 15 min. Nurses assist the SSC process and carry out empty breast sucking (suck on empty breast) training for 5 to 10 min. In case of non-skin contact, a pacifier shall be used for sucking before tube feeding. SSC will be carried out at least once a day for 1 h, and monitoring should be done at the same time. The infant will be fed by a nasogastric tube. At 32 weeks’ gestation, attempts will be made to feed the infant by the bottle, using bottles specially designed for preterm infants. Before feeding, non-nutritive sucking will be conducted with a pacifier for 5 to 10 min. The number of oral feeding attempts will be gradually increased according to the oral feeding schedule. Achievement of full oral feeding is achieved when the daily amount of oral feeding milk reaches 75% of the required volume, no gavage feeding is needed for 48 h, and the daily body weight increases by 10–15g/kg/day. At this point, the infant is weighed, SSC is ceased, and the HAD questionnaire is sent to the mother for the third time for completion within 24 h. The weight will be measured on this day. On the day of discharge, the infant is weighed, and parental satisfaction will be assessed by EMPATHIC-N [38]. And the PIBBS scale will be used to evaluate the breastfeeding behavior of preterm infants on discharge day. The HAD questionnaire is sent to the mother for the fourth time at this time for completion within 24 h. Research team members will complete the organization and entry of the infant’s clinical course in the hospital, and a second-team member will be responsible for verifying the collection and entry of the information. After discharge, the rate and mode of breastfeeding will be followed up by breastfeeding education nurses at 3 and 6 months corrected gestational age.

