### Statistical analyses

All analyses will be performed using SPSS 22.0 (IBM SPSS Statistics, IBM Corporation, Chicago, IL). The two-tailed significance level will be set to *P* < 0.05. An intention-to-treat (ITT) analysis will be used for the outcomes. For primary outcome analyses, the generalized linear model (GLM) will be used to test the difference of the time to achieve full oral feeding (days) between the groups, and the estimated means and two-sided 95% confidence intervals (CI) will be derived. The clinical factors including gestational age, sex, birth weight, admission age, oxygenation indices (OI), etc. will be adjusted in the covariate-adjusted analysis of the primary outcome by the GLM model. If any subjects dropped off from the primary endpoint, modified ITT analysis will be performed by using the available subjects.

All secondary outcomes will be analyzed by GLM. Binary secondary outcomes will be summarized as absolute numbers and percentages, and the difference and its 95% CIs between the two groups will be estimated. The continuous outcome will be presented as means and standard deviations (SD) and be analyzed with the same strategy and method with that is used for the primary outcome.

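### The second maternal HAD questionnaire is triggered by different milestones in the two arms, so a between-arm comparison at that wave mixes treatment with the infant's stage and postnatal time

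*Protocol article*

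**What the plan says.** All places are in the protocol article.

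- **First HAD, both arms** (Management before procedure): around the day of admission, the education nurse sends the "questionnaire to the mother for completion within 24 h by WeChat".
- **Second HAD, control arm** (The control group): "When oral feeding is commenced, the infant’s mother will be informed by telephone that this has started". Then: "At this point, the HAD questionnaire is sent to the mother for a second time for completion within 24 h".
- **Second HAD, intervention arm** (The intervention group): "After the withdrawal of mechanical ventilation, the infant will be assessed for 12 to 24 h". When the infant is stable, "the mother will be invited to enter the NICU, and the HAD questionnaire will be sent to the mother for the second time". The infant is still tube-fed at this stage. Bottle feeding is a separate, later step: "At 32 weeks’ gestation, attempts will be made to feed the infant by the bottle".
- **Third and fourth HAD** (both group sections): sent at full oral feeding and at discharge in both arms.
- **Outcome** (Secondary outcomes): anxiety and depression in parents is the last item listed, with no wave or time point named.
- **Analysis** (Statistical analyses): "All secondary outcomes will be analyzed by GLM". Continuous outcomes follow the primary outcome's approach. The adjusted version of that approach names gestational age, sex, birth weight, admission age and oxygenation index, in a list left open at the end.

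**The concern.** Randomisation makes the arms comparable when they are measured at comparable times. Here the measurement time of the second HAD is set by the arm itself. One mother answers when she is first invited to the bedside of a tube-fed infant who has just come off ventilation. The other answers after a telephone call saying that oral feeding has begun. A difference in scores could come from the intervention, from the different stage of the infant's course, from the different number of days since birth, or from the event that prompted the form.

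The intervention arm has a further problem. Its second form is sent at about the first skin contact, so the score can carry little of the effect that the trial wants to detect. A difference at this wave could be read as a treatment effect when it is not one, and a null result there would say little about the intervention.

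Adjusting for infant factors fixed at birth or admission does not help, because the difference in timing arises after randomisation and by design.

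**Working it through.** **1. The four waves side by side**

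| Wave | Control | Intervention | Same milestone? |
|---|---|---|---|
| 1 | Admission | Admission | Yes |
| 2 | Start of oral feeding | Infant stable after 12 to 24 h assessment off ventilation; mother invited in | No |
| 3 | Full oral feeding | Full oral feeding | Yes |
| 4 | Discharge | Discharge | Yes |

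Only wave 2 departs from the pattern.

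**2. How far apart are the two milestones?** The control section gives no gestational age for the first oral feed. The 32-week figure stands only in the intervention section. If control infants also started at about 32 weeks (an assumption), the gap would be 32 minus the gestational age at which the intervention infant is stable off ventilation:

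- stable at 28 weeks: 32 − 28 = 4 weeks
- stable at 30 weeks: 32 − 30 = 2 weeks
- stable at about 32 weeks: near 0

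The gap therefore varies by infant and cannot be fixed from the documents.

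**3. The plan's own figure.** The only sample size is for the primary outcome: difference 4.0 days, SD 7.0, two-sided alpha 0.05, 90% power. The noncentral t calculation gives power 0.8985 at 65 per arm and 0.9029 at 66, so the stated 66 reproduces. With 10% dropout, 66/0.9 = 73.3, rounded up to 74, as stated. This point does not depend on that calculation. It only uses 66 per arm as the number analysed.

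**4. What a timing difference could do (illustration only).** The documents give no HAD mean, SD or trend. Assume no treatment effect and a drift in HAD of 0.05 to 0.2 SD per week.

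- Spurious difference d (in SD) = drift × gap.
- Noncentrality = d × √(66/2), with 130 degrees of freedom. For d = 0.2 it is 0.2 × 5.745 = 1.149.

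Each cell shows d and the rejection rate of a nominal 5% two-sided test:

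| Drift per week | 1 week | 2 weeks | 3 weeks | 4 weeks |
|---|---|---|---|---|
| 0.05 SD | 0.05; 5.9% | 0.10; 8.8% | 0.15; 13.7% | 0.20; 20.7% |
| 0.10 SD | 0.10; 8.8% | 0.20; 20.7% | 0.30; 40.2% | 0.40; 62.6% |
| 0.20 SD | 0.20; 20.7% | 0.40; 62.6% | 0.60; 92.8% | 0.80; 99.5% |

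With a gap or drift of zero the rate is the nominal 5%. The range is too wide to support any single figure.

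**5. Would baseline adjustment cure it?** No. Adjusting for the admission score multiplies the residual variance by 1 − r². For assumed correlations of 0.3, 0.5 and 0.7 the factor is 0.91, 0.75 and 0.51. The timing difference d stays while the standard error shrinks. With d = 0.2 SD the rejection rate moves from 20.7% to 22.3%, 26.1% and 35.8%. Adjustment helps precision at waves with matched timing and does nothing for the bias at wave 2.

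**The case against.** The strongest reply is that the protocol never says the second wave will be tested. No HAD time point is named, and two post-randomisation waves with matched milestones are available, so a like-for-like comparison exists. That stands. A reader might infer that the GLM will compare the second forms as one visit, but the text does not say so. What remains is that the text does not exclude it either, and the arm-specific trigger is a data-collection rule that an analysis plan cannot undo afterwards.

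Three other stronger readings are tempting and are not supported:

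- *That the admission score is left out of the model.* The covariate list is open-ended, so the score is neither named nor excluded. Covariates for one secondary outcome are commonly left to an analysis plan, which is not shown here.
- *That the milestones are about two weeks apart, with control later.* This carries the 32-week figure across from the intervention arm and assumes an age at weaning. For infants ventilated until near 32 weeks the gap may vanish.
- *That the control mother alone hears good news.* An invitation to the bedside of a newly stable infant could be described in the same way. The triggering events differ, but the direction of any effect on the score is unknown.

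Nor do the documents show that the admission form is completed after allocation, so there is no defect of that kind to correct.

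**Conclusion.** The point holds for the second wave. The two group sections set different triggers for the same numbered questionnaire, and a between-arm difference at that wave cannot be read as a treatment effect. This follows from the text and needs no assumption.

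The size of the bias cannot be derived. The rejection rates of about 6% to 99% rest on assumed drifts of 0.05 to 0.2 SD per week and gaps of 1 to 4 weeks. With a gap near zero, the excess from drift disappears.

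The consequence is limited to one of four waves of one secondary outcome, which the abstract's list of secondary outcomes does not include. The primary outcome and the sample size are untouched. It merits correction because the remedy costs almost nothing. The missing mention of the admission score is a lost opportunity for precision, to be settled in the analysis plan, and is not an error in this document.

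**What to change.** 1. **Reconcile the two group sections** so that the second HAD goes out at the same milestone in both arms, or at both milestones in both arms. The form is sent by WeChat, so this means changing an electronic trigger or, at most, adding one short form per mother.
2. **Where data are already collected**, base between-arm HAD inference on the third and fourth waves and report the second descriptively by arm, with the infant's postnatal age at completion. Recruitment was due to end on July 1, 2021, before the article appeared on September 17, 2021, so this may be the only remedy left for most mothers. It costs one sentence in the analysis plan, written before the HAD data are compared by arm.
3. **Secondary, for precision only:** name the admission HAD score, already collected, as a covariate for the later HAD comparisons. This costs one model term. It should not be presented as a cure for the timing difference.

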### The nutritional protocol in the two groups

Direct breastfeeding can be carried out after discharge without adding a fortifier. For both groups, lactation consultants will deliver information on the benefits of breastfeeding to mothers at admission, provide breastfeeding practice before discharge, provide neonatal follow-up after discharge, and provide breastfeeding guidance at the outpatient clinic. Breast milk fortification begins when the amount of breast milk reaches 50~80 ml/(kg day). A breast milk fortifier needs to be used immediately after configuration.

### Outcomes and measurements

#### Primary outcome

The time from the first oral feeding to full oral feeding (days) [39]: When the daily amount of orally fed milk reaches 75% of the required volume, no gavage feeding is needed for 48 h, and the daily body weight increases by 10–15g/kg/day, the infant is defined as having reached full oral feeding.

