**Methods:**

This is a single-center, randomized controlled clinical trial conducted in the NICU and designed according to the SPIRIT Statement. The subjects included in the study are premature infants born between April 2020 and July 2021 with a gestational age of ≤30 weeks, birth weight of <1500 g, admission age of <72 h, and absence of congenital malformations. Those with oxygenation indices of >40 and those born to mothers with poor verbal communication skills will be excluded. A sample of 148 infants is needed. The infants will be randomized to the intervention (skin contact combined with mother’s breastfeeding model) or control group (routine pacifier sucking training model). The primary outcome is the time required to achieve full oral feeding. The secondary outcomes are the breastfeeding abilities of preterm infants as assessed by the Preterm Infant Breastfeeding Behavior Scale (PIBBS), breastfeeding rates at 3 and 6 months corrected gestational age, complication rates, duration of oxygen requirement, days of hospital stay, and satisfaction of parents.

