Non-nutritive sucking by sucking the mother’s “empty” breast is more conducive to promoting the development and maturity of sucking than using a pacifier. This sucking is completed at the source of nutrition without affecting nutrient intake. When sucking the “empty” breast, the baby showed that the nipple was tightly locked and fixed on the nipple. Time spent in active sucking, sucking burst, and swallowing were all longer and feeding behavior was more mature [25]. Skin-to-skin contact (SSC) is a maternal and infant practice recommended by the World Health Organization (WHO). It has been proven that SSC plays an important role in both infants and mothers [26]. The sleep or wakefulness behavior of infants receiving SSC is more organized, and they have more time in quiet sleep and in the alert awake state [27, 28]. SSC contributes to the development of the infant’s nervous system [28–30], and it has been reported that infants receiving SSC have shorter hospital stays and lower infection severity [31, 32]. Infants who received SSC had higher intelligence and better psychomotor development at 12 months corrected gestational age [30]. From the breastfeeding perspective, SSC can improve the production of breast milk, help establish breastfeeding, prolong the duration of breastfeeding, enhance the willingness to breastfeed [33–35], and help to reduce stress in new mothers [35].

In the process, the mother expresses breast milk prior to tube feeding and tube feeding is combined with skin-to-skin contact. The mother manually drips the breast milk onto the baby’s lips, and the baby tastes and becomes familiar with breast milk while being tube-fed. Non-nutritive sucking on the breast is conducive to the transition from tube feeding to breastfeeding, which is in turn conducive to breastfeeding [36]. As the infant matures, the infant will naturally approach the breast during SSC, which triggers instinctive breastfeeding behavior, promotes the coordination of sucking and swallowing, starts the first nutritive sucking earlier, and improves the duration of sucking, so as to satisfy the infant’s instinctive desire to suck.

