### Sample size

Sample size calculation is performed based on the primary outcome that is the time to achieve full oral feeding. The average days to achieve full oral feeding was 14 days with a standard deviation of 7 days in the control group according to the previous study. The time for the intervention group to achieve full oral feeding was 4 days shorter than that of the control group [48]. The sample size of 66 in each group could achieve 90% power to detect a difference of 4.0 between the groups with estimated group standard deviations of 7.0 and with a significance level (alpha) of 0.05. At least 74 subjects will be recruited in each group considering a 10% drop rate. Sample size calculation was performed by Power Analysis & Sample Size ® software version 16.0 (NCSS, LLC. USA).

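### The primary outcome is timed from the first oral feed, which comes after randomisation, so a shorter interval alone cannot show that infants reached full oral feeding sooner

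*Protocol article*

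**What the plan says.** The Primary outcome section of the protocol article is the only place that gives the clock a start: "The time from the first oral feeding to full oral feeding (days"). Elsewhere the wording has no origin. The abstract says "The primary outcome is the time required to achieve full oral feeding", and the Sample size section describes its calculation as "based on the primary outcome that is the time to achieve full oral feeding".

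The two arms are described differently at the point where the clock starts. For the intervention group: "At 32 weeks’ gestation, attempts will be made to feed the infant by the bottle". For the control group the text says what is used, "Feeds are given with a special bottle designed for preterm infants", and what follows the start, "When oral feeding is commenced, the infant’s mother will be informed by telephone that this has started", but not what triggers it. Both texts refer to an oral feeding schedule, but only for increasing feeds once they have begun. The schedule is not reproduced.

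Under Randomization, envelopes are opened after parental consent. Infants enter at 30 weeks or less, admitted before 72 h of age. Study setting and design calls the trial open-label. Statistical analyses specifies a generalized linear model on days, and the covariates it names are baseline factors.

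**The concern.** Randomisation balances the arms at allocation. It does not protect a time origin that arises later and that treatment, or staff who know the allocation, may move. The interval then mixes two things: a change in when infants reach full oral feeding, and a change in when the first feed was offered. A later first feed in the intervention arm could look like a benefit with no gain to the infant. An earlier one could hide a real gain.

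The Background gives some reason to ask the question, since it expects that skin contact at the breast "starts the first nutritive sucking earlier". The stake is the main conclusion: a significant shortening of the interval could be reported as infants feeding fully by mouth sooner when the primary analysis alone does not establish that.

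**Working it through.** **Inputs.** From Sample size: difference 4.0 days, SD 7.0 in each group, alpha 0.05, power 90%, 66 per arm, 74 after 10% dropout. From Statistical analyses: a two-tailed test. The shifts in first feed used below are assumptions; the article gives no timing of first feeds by arm.

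**The plan's own figure.**
- Normal approximation: n = 2 × (1.960 + 1.282)² × 7² / 4² = 64.4, so 65 per arm.
- Two-sample t-test (noncentral t): power 0.899 at 65 per arm and 0.903 at 66. This gives the stated 66.
- Dropout: 66 / 0.90 = 73.3, so 74. The sample size arithmetic is not at fault.

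**How the clock enters the contrast.** Let S be the mean age at first oral feed and F the mean age at full oral feeding, with subscripts C (control) and I (intervention). The apparent benefit is

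(F_C − S_C) − (F_I − S_I) = (F_C − F_I) + (S_I − S_C).

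The first term is the gain in reaching full feeding. The second is the shift in the clock's start, and it enters one for one.

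**Precision at 66 per arm.** SE = 7 × √(2/66) = 1.22 days. The smallest significant difference is 1.98 × 1.22 = 2.41 days.

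**(a) No gain in age at full feeding; intervention first feed later by the assumed shift.**

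| Shift (days) | Apparent benefit (days) | Chance of P < 0.05 |
|---|---|---|
| 0 | 0 | 5% |
| 1 | 1 | 13% |
| 2 | 2 | 37% |
| 3 | 3 | 69% |
| 4 | 4 | 90% |

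**(b) True gain of 4 days in age at full feeding; intervention first feed earlier by the assumed shift.**

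| Shift (days) | Observed benefit (days) | Chance of P < 0.05 |
|---|---|---|
| 0 | 4 | 90% |
| 1 | 3 | 69% |
| 2 | 2 | 37% |
| 3 | 1 | 13% |
| 4 | 0 | 5% |

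**Sensitivity to the SD.** For a 2-day shift under (a), the chance of significance runs from 48% at SD 6 to 25% at SD 9.

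**If start and end move together in part.** Suppose the intervention's first feed is 4 days later and full feeding is 2 days later as a result. The apparent benefit is −2 + 4 = 2 days, although those infants reached full feeding 2 days later.

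**Can the planned model remove the shift?** The named covariates are measured at or near entry, so they cannot. Adding age at first feed would condition on a post-randomisation variable.

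**The case against.** Much of the case on the other side stands.

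- **The missing control trigger is silence, not a different rule.** This is a condensed article, the trial procedure figure is not visible, and both arms cite a feeding schedule that may set a common start. The Discussion treats gestational age as the usual basis for starting oral feeds, though it also argues that feeding need not wait until 32–34 weeks. A reader might infer that the arms start the clock under different rules. The documents do not support that: one start is written and the other is not shown.
- **The intervention may not advance the first bottle feed.** The Background phrase on nutritive sucking is a general statement about behaviour at the breast. In the intervention text, breast sucking is on an empty breast, the infant is tube-fed, and bottle attempts are tied to 32 weeks. Followed strictly, that limits how far earlier readiness can move the start.
- **The interval is a legitimate outcome.** The title and the stated objective speak of shortening the process, which fits the transition from tube to full oral feeding. It would be too strong to infer that the trial cannot answer its own question.
- **The shifts are hypothetical.** Table (a) is the design's power curve applied to an assumed shift, with the date of full feeding held fixed. If start and end move together, the artefact is smaller.
- **There is a partial safeguard.** Length of stay, counted from NICU admission, is a secondary outcome.

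What these points do not remove is the origin itself. Even under a shared start rule, the first feed follows allocation and can be influenced by unblinded staff. If start and end move fully together, the interval shows no difference even when infants reach full feeding days earlier. Keeping the outcome analysts unaware of allocation does not cover the bedside decision.

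**Conclusion.** The point holds in a limited form. The primary interval starts at a post-randomisation event in an open-label trial, the article states when bottle attempts start in one arm only, and baseline adjustment cannot correct a between-arm shift. A shorter interval is therefore evidence about the transition, not by itself evidence that infants reached full oral feeding sooner.

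The size is conditional. Each day of unmatched shift moves the estimate by one day, against an SE of 1.22 days and a planned effect of 4 days. The rates of 37%, 69% and 90% rest on SD 7, 66 per arm, assumed shifts of 2, 3 and 4 days, and an unchanged date of full feeding. Nothing in the documents shows that a shift will occur, or how large it would be. This should be fixed because the remedy is cheap and protects the main claim; it does not show that the design fails.

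**What to change.** - Add a co-reported key analysis with an origin that treatment cannot move: postmenstrual age at full oral feeding, or days from randomisation or birth to full oral feeding adjusted for gestational age at birth.
- Report postmenstrual age at first oral feed by arm, so that readers can see any shift in the start.
- State in advance that the intervention will be said to bring infants to full oral feeding sooner only if the fixed-origin analysis agrees with the interval result.
- Make the fixed-origin measure the primary outcome if its SD supports the sample size; that would be preferable.
- Reconcile the control and intervention texts on when the first oral feed occurs in each arm. Which clinical rule applies is for the trial team.
- State the same time origin in the abstract, Sample size and Statistical analyses sections as in the Primary outcome section.

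The cost is one extra analysis from feeding data that the article says are already recorded. The drawback is that precision for the new origin is unknown: the documents give no SD for it, and the 14-day mean and 7-day SD cannot be assumed to carry over.
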